Second, patients with an increased risk for an adjustment disorder (i.e. HADS score > =11, DT > =4 or work/school/study problems, family or social problems, emotional problems, fatigue or wanting to talk to a psychologist or social worker as reported on the problem list) will be invited for a diagnostic interview by a registered psychologist, psychotherapist or psychiatrist trained in clinical care for cancer patients with an adjustment disorder (further called healthcare professional (HCP)). During this diagnostic interview by telephone or face to face the presence of an adjustment disorder will be investigated. HCPs will follow the Dutch guideline on adjustment disorder diagnosis [36]. The guideline committee recently defined adjustment disorder in patients with cancer as the combination and interaction among three pillars, namely stressors (e.g. cancer diagnosis, fear of cancer recurrence, physical changes in a patients’ appearance), insufficient protective factors (e.g. resilience, physical health, meaning, social support, autonomy), and the experience of symptoms (e.g. anxiety, depression, fatigue, relation problems, limited work productivity) [3]. During the diagnostic interview, the HCP will also complete a form on sociodemographic (age, gender) and clinical (tumour site, stage, phase of cancer (acute/chronic/palliative), time since diagnosis, treatment modality) parameters, and a form on stressors experienced, protective factors, symptoms experienced and actual psychologic diagnosis. To monitor the robustness of this diagnosis, the diagnostic interview will be audio recorded in case the patient provides specific informed consent on this matter. Approximately 5 % of the total diagnostic interviews will be scored twice (adjustment disorder yes/no).

Additionally, all participating HCPs will be asked to complete a questionnaire on type of care (primary or secondary care), profession and training, and years of experience in working with cancer patients.

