### Part 2: tailored psychological intervention

The psychological intervention investigated in this proposed project follows the Dutch guideline on diagnosis of adjustment disorders [36] and consists of 3 modules. Module 1 encompasses a maximum of 3 sessions on psycho-education with an HCP. Module 2 and 3 encompass both a maximum of 6 sessions. Module 2 and 3 can consist of all evidence-based interventions outlined in the guideline on adjustment disorders, such as cognitive behavioural therapy, mindfulness, group interventions, online interventions or pharmacotherapy [3]. Depending on the wishes and needs of the patient a specific type of therapy per module will be offered to the patient (tailored treatment) [37].

After each last session of a module the HCP will assess in accordance with the patient if another module is needed. To support this assessment the patient will complete the HADS during this session, following the guideline on diagnosis of adjustment disorders [36]. When sufficiently effective, only the short psychological treatment module 1 will be provided. The longer treatments (module 2 or module 3) will only be offered if the previous psychological treatment module was insufficiently effective, so the 3 modules will be provided as a continuum.

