### Sample size

The sample sizes of Part 1 and 2 depend on each other. To demonstrate an effect size in Part 2 of 5 points on the HADS as statistically significant, anticipating a standard deviation of 11 (i.e. two times the baseline standard deviation of the HADS), 77 participants in each condition are needed at follow-up (power 80%, significance level 5%). Anticipating a drop-out rate of 25% between baseline and 6 month follow-up, 103 participants per condition, thus 206 in total, need to be included at baseline. Estimating a willingness to participate in this RCT of 60%, 343 patients will need to be approached to participate in the RCT in Part 2 [49]. Taking into account a prevalence rate of adjustment disorders of 11% as estimated by Mehnert et al. [7], 3119 cancer patients need to be screened in Part 1 to identify 343 patients with adjustment disorders. Anticipating a response rate of 50%, 6238 patients need to be approached for the screening.

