### Statistical analysis

In Part 1 and Part 2 quantitative analyses will be performed using the IBM Statistical package for the Social Science (SPSS) version 25 (IBM Corp., Armonk, NY USA) and STATA version 14 Descriptive statistics will be generated for all socio-demographic and clinical characteristics and outcome measures. Chi-square tests, independent t-tests and Mann-Whitney tests (in case of non-normality of the measure) will be used to analyse whether randomization resulted in comparable patient groups. Analyses will be performed according to the intention-to-treat principle. A *p*-value < 0.05 will be considered significant.

Part 1 aims to investigate the prevalence of having an adjustment disorder, to investigate the uptake of psychological treatment among cancer patients with an adjustment disorder and to investigate its determinants. Determinants of having an adjustment disorder or uptake of psychological care will be entered one-by-one to the logistic regression model using a p-value for entry of 0.05. Potential determinants include scores on the patient-reported outcomes, socio-demographic, and clinical characteristics of the patient, as well as HCP characteristics. Part 2 aims to investigate the effectiveness of the intervention on the primary outcome measure (HADS) with the use of linear mixed models. The linear mixed model will contain a fixed effect for arm/group, time and their two-way interaction, and a random effect for subject. A significant (*p* < 0.05) two-way interaction indicates a difference in effectiveness between the intervention and the control group. In that case, post-hoc effect sizes, at 3 and 6 months follow-up, will be calculated using Cohen’s d.

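### Healthcare-professional characteristics are tested in Part 1 without allowing for clustering by professional, and the Part 2 primary model ignores therapist clustering in the intervention arm

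*Protocol article*

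**What the plan says.** **Part 1.** Under Part 1: prevalence and reach, patients who screen positive are invited to a diagnostic interview, and the interviewing HCP decides whether an adjustment disorder is present. HCP data are collected once per professional: "all participating HCPs will be asked to complete a questionnaire on type of care", and also on profession, training and experience. Under Statistical analysis, determinants of diagnosis and of uptake are entered singly into a logistic regression with an entry threshold of p=0.05. The candidates are patient-reported scores and patient characteristics, "as well as HCP characteristics". No term for the HCP is mentioned.

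**Part 2.** Module 1 is given by an HCP. Modules 2 and 3, offered only when the previous module has not helped enough, can take several forms, "such as cognitive behavioural therapy, mindfulness, group interventions, online interventions or pharmacotherapy". Control patients receive the programme only after the 6-month waiting period, when the last measurement is due. The primary model is listed term by term: fixed effects for arm, "time and their two-way interaction, and a random effect for subject". Under Sample size, "77 participants in each condition are needed at follow-up", with no design effect. HCP is not a stratification factor.

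**The concern.** Patients who share an HCP may have correlated outcomes. In Part 1 the link is direct, because the same professional produces the outcome (the diagnosis) and supplies the predictor (own profession, training, setting, experience). The Part 2 inclusion procedure also has the HCP introduce the trial to the patient, so uptake may differ by HCP too. For a predictor that is constant within an HCP, the information lies in the number of HCPs, whereas an ordinary logistic regression counts patients. Chance differences in diagnostic threshold between a few professionals could then pass the p<0.05 entry rule and be reported as an effect of training or setting. The Discussion itself says the disorder is poorly conceptualised and that this may limit diagnostic precision, so variation between interviewers is plausible.

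In Part 2, therapy can create correlation among intervention patients who share a therapist or group, and no such correlation arises among controls during follow-up. A model whose only random effect is the subject treats all patients as independent, which can make the arm-by-time test somewhat too liberal.

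**Working it through.** **The plan's own figure.** Inputs from Sample size: "To demonstrate an effect size in Part 2 of 5 points on the HADS as statistically significant", "anticipating a standard deviation of 11", 80% power, 5% significance.

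n per arm = 2 × (1.96 + 0.8416)² × 11² / 5² = 75.98, so 76. The t-based version gives 76.95, so 77. After 25% dropout, 77 / 0.75 = 102.7, so 103 per arm and 206 in total; 206 / 0.6 = 343 patients to be approached. The stated figures reproduce as two-sided figures with no allowance for clustering.

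**Assumed inputs.** The protocol gives no number of HCPs, no caseload (m) and no intraclass correlation (ICC). The results below are therefore ranges.

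**Part 1, by formula.** For an HCP-level covariate the variance is understated by DE = 1 + (m − 1) × ICC, and the true type I error is 2 × [1 − Φ(1.96/√DE)].

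- ICC 0.05, m = 10: DE = 1.45, 1.96/1.204 = 1.628, error about 10%.
- ICC 0.05, m = 30: DE = 2.45, 1.96/1.565 = 1.252, error about 21%.
- ICC 0.02, m = 10 to 30: DE = 1.18 to 1.58, error about 7 to 12%.

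**Part 1, by simulation.** Ordinary logistic regression was fitted to HCP-clustered data in which the covariate had no effect (1000 runs per scenario; Monte Carlo standard error at 5% is √(0.05 × 0.95/1000) = 0.7 percentage points). The ICC is on the latent logistic scale. The uptake rows use the protocol's 343 patients and 60%. The diagnosis row assumes 1000 interviews, 34% of them positive.

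| Outcome | HCPs | ICC 0.02 | ICC 0.05 | ICC 0.10 |
|---|---|---|---|---|
| Uptake, N = 343 | 20 | 6.6% | 11.4% | 18.9% |
| Uptake, N = 343 | 40 | 6.0% | 9.0% | 12.9% |
| Uptake, N = 343 | 80 | 6.2% | 7.2% | 7.7% |
| Diagnosis, N = 1000 | 40 | 9.5% | 15.3% | 24.8% |

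In the same scenarios a patient-level covariate unrelated to HCP was significant in 3.8 to 6.5% of runs, that is, near 5%.

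**Part 2, by formula.** One arm is clustered, so the standard error is understated by the factor √[(1 + DE)/2].

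- ICC 0.01, m = 4: DE = 1.03, factor 1.01, error 5.2%.
- ICC 0.05, m = 8: DE = 1.35, factor 1.084, error 7.1%. A test with the correct standard error has 74.0% power, against 80.5% for 77 per arm with no clustering. Restoring 80% needs 77 × 1.175 = 90.5, so 91 per arm at follow-up (244 in total at baseline).
- ICC 0.10, m = 8: DE = 1.70, factor 1.162, error 9.2%, power 68.0%, 104 per arm (278 in total).

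**Part 2, by simulation of the planned interaction test.** There were three time points, 77 per arm, complete data, an assumed within-subject correlation of 0.5, and a cluster effect at half size at 3 months and full size at 6 months (8000 runs per scenario; Monte Carlo standard error at 5% about 0.24 percentage points). Each cell gives formula / simulation.

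| ICC | m = 2 | m = 4 | m = 8 |
|---|---|---|---|
| 0.02 | 5.1% / 5.1% | 5.3% / 5.3% | 5.8% / 5.4% |
| 0.05 | 5.3% / 5.0% | 5.9% / 5.6% | 7.1% / 6.5% |
| 0.10 | 5.6% / 5.9% | 6.8% / 6.0% | 9.2% / 8.2% |

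With no clustering the simulation gave 4.9 to 5.3%. The formula describes a comparison at one time point. The simulation, which is closer to the planned test, gives mostly smaller values.

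**The case against.** **The article is condensed.** The logistic model gets a few lines, and a full analysis plan could add a random intercept or robust errors. This stands in part. But the article does fix HCP-level predictors together with a p-value entry rule, and it lists the primary model term by term. Followed as written, both omit the HCP.

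**Every magnitude is assumed.** This stands. With 80 HCPs the Part 1 inflation for uptake is small, and in Part 2 an ICC of 0.01 to 0.02 with small caseloads is negligible. The 9.2% needs every intervention patient to sit in a cluster of eight at ICC 0.10, which is hard to square with a programme that may end after three sessions.

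**The determinants analysis is exploratory.** That is fair, and it limits the weight of the point. Still, Strengths and limitations presents the analysis as a way to identify risk groups.

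**About 5% of interviews are scored twice.** This checks agreement on the diagnosis. It does not correct the standard errors of HCP determinants.

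**The Part 2 cluster is not well defined.** Modules can differ in provider and format, and nothing says that the diagnosing HCP also treats. This stands, and it is the reason to ask for a sensitivity analysis and not a new primary model.

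**Stronger readings are tempting.** A reader might infer that patients are nested in therapy groups in both parts, or that standard errors are too small throughout. The protocol does not support either reading. Part 1 has no therapy groups, only interviewing HCPs and only for patients who screen positive. In Part 2 groups are one option among several. Patient-level determinants keep close to 5%. An HCP effect common to both arms, such as that of the diagnosing HCP, does not shrink the arm-by-time standard error, and leaving it out tends to be conservative.

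**Conclusion.** The point holds in two limited forms.

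The main one is Part 1. Tests of HCP-level determinants are anti-conservative if HCPs differ in diagnosing or referring, with a type I error of about 6 to 25% at nominal 5%. This rests on assumed ICCs of 0.02 to 0.10, 20 to 40 HCPs and, for the upper end, an assumed 1000 interviews.

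The second is Part 2. The intervention arm is partially nested while the primary model has a subject effect only. The true type I error is about 5 to 9% by formula and 5.0 to 8.2% in simulation of the planned test, so the effect runs from nil to modest. The documents do not support a conclusion that the primary analysis is invalid.

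**What to change.** **Part 1.** Record the HCP's identity on each interview form, which the HCP already completes. Test HCP characteristics among interviewed patients (for uptake, among diagnosed patients) with a random intercept for HCP or with standard errors clustered by HCP. Report the between-HCP variance. It indicates how far diagnosis depends on the interviewer, although it also contains differences in case mix.

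**Part 2.** Keep the stated primary model and prespecify a sensitivity analysis with a random effect for the treating HCP or therapy group that acts in the intervention arm only, with small-sample degrees of freedom. State the clustering rule in advance: for example the module 1 HCP, with patients who never start treated as clusters of one.

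**Cost.** One identifier per record, a short addition to the analysis text and slightly wider intervals. No further data collection from patients is needed.

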### Part 2: study population and inclusion procedure

Patients diagnosed with an adjustment disorder in Part 1 of this study will be invited to participate in Part 2 (the RCT). Patients will be first introduced to the study by the HCP. The coordinating researcher of the study will further inform interested patients by phone. Also, the patient information form and informed consent of Part 2 will be sent to the patient. After obtaining informed consent, the patient is asked to fill in the baseline questionnaire via the internet or using paper-and-pencil. After completing the baseline questionnaire, the patient will be randomized into either the intervention group (start of the tailored psychological intervention within 3 a 4 weeks) or the waitlist control group (receive a tailored psychological intervention after a waitlist period of 6 months). All patients will be asked to complete questionnaires before randomization (T0), and 3 (T1) and 6 months (T2) after randomization. In case of non-response to these questionnaires a reminder letter and a paper-and-pencil questionnaire will be sent after 3 weeks. If they do not respond to this reminder, they will be contacted by telephone within 2 weeks. Reasons for dropouts will be registered. Data will be collected using the PROFILES system.

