### Part 2: outcome assessments

The primary outcome of Part 2 is psychological distress. Secondary outcomes are Mental Adjustment to Cancer and health-related quality of life. In addition, the cost-utility and budget impact of the psychological intervention will be investigated (Table 1). To determine cost-utility and budget impact, Quality-Adjusted Life-Years (QALYs) and costs will be measured. For the cost-utility and budget impact analyses from a societal perspective, intervention costs, healthcare costs, costs of the patient and his/her family (e.g. informal care costs and travel costs) and costs in other sectors (e.g. productivity losses) will be collected. The healthcare perspective will only include intervention costs and healthcare costs and the insurer perspective will only include costs reimbursed by the healthcare insurance company.

**Table 1 Tab1:** Outcome measures and used instruments

Part	Outcome	Outcome measure	Instrument
1	Primary outcome	Reach: prevalence of adjustment disorder (yes/no) and uptake of the tailored psychological intervention (yes/no)	Screening (DT, problem list and HADS) and interview
1	Other collected measurements	Fatigue	CIS
2	Primary outcome	Psychological distress	HADS
2	Secondary outcomes	Mental adjustment to cancer	MAC
		Health-related quality of life	EORTC-QLQ-C30
		Cost-utility measures	
		Medical utilization costs Informal care costs	iMCQ questionnaire iMCQ questionnaire
		Productivity losses	iPCQ questionnaire
		Quality adjusted life-years	EQ-5D-5 L
1–2	Other collected measurements	Socio-demographic and clinical characteristics	Study specific questionnaire
		Healthcare professional characteristics	Short questionnaire on type of care

*HADS* Hospital Anxiety and Depression Scale, *CIS* Checklist Individual Strength, *MAC* Mental Adjustment to Cancer, *EORTC QLQ-C30* European Organization for Research and Treatment of Cancer Quality of Life Questionnaire, *iMCQ* Medical consumption questionnaire, *iPCQ* Productivity cost questionnaire, *HCP* healthcare professional

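### Effect sizes at 3 and 6 months are calculated only if the arm-by-time interaction is significant, no primary time point is named, and the stated 80% power was not calculated for an overall interaction test

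*Protocol article*

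**What the plan says.** All references are to the protocol article.

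- **Outcome** (Part 2: outcome assessments): "The primary outcome of Part 2 is psychological distress". No assessment time is attached to it there, in Table 1, in the abstract, or under Primary outcome measures.
- **Visits** (Part 2: study population and inclusion procedure): "All patients will be asked to complete questionnaires before randomization (T0), and 3 (T1) and 6 months (T2) after randomization".
- **Model** (Statistical analysis): "The linear mixed model will contain a fixed effect for arm/group, time and their two-way interaction, and a random effect for subject". Whether time enters as a category or as a linear term is not stated.
- **Decision rule** (same section): a significant "two-way interaction indicates a difference in effectiveness between the intervention and the control group", with p<0.05 as the criterion.
- **Effect sizes** (next sentence): "In that case, post-hoc effect sizes, at 3 and 6 months follow-up, will be calculated". The measure is Cohen's d.
- **Sample size** (Sample size): the target is a HADS difference of 5 points, with a planning SD of 11 that the article describes as double the SD at baseline. The resulting requirement is given as "77 participants in each condition are needed at follow-up (power 80%, significance level 5" per cent. The 25% drop-out allowance runs to the 6-month follow-up and gives 103 per arm, 206 in total.

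**The concern.** Two features of the stated rule cause trouble.

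First, the effect sizes are conditional on significance. If the interaction reaches p<0.05, the Cohen's d values come from a subset of possible trials in which the estimates tend to be too large. If it does not, no effect size is called for. The article says under Implementation and clinical practice that the trial was requested to support a reimbursement decision. For that purpose an effect size with its interval is most needed when the test is not significant, because it separates a trial that excludes a worthwhile effect from one that is merely imprecise.

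Second, the test and the sample size rest on different quantities. The sample size is one two-group difference at one follow-up, and the drop-out horizon points to 6 months. The analysis tests an interaction across three visits and names no time point. If time is categorical, a difference at 3 months that has gone by 6 months satisfies the rule just as a lasting one does.

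**Working it through.** **1. Reproduce the sample size.** Inputs from Sample size: difference 5, SD 11, power 80%, significance level 5% (two-sided assumed; one-sided would give 60 per arm).

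- Standard error of the difference at 77 per arm: 11 × √(2/77) = 1.773. Ratio 5/1.773 = 2.82.
- Two-sample t-test power: 80.0% at 77 per arm and 79.5% at 76. The normal approximation gives 80.5% at 77.
- Drop-out: 77/0.75 = 102.7, so 103 per arm and 206 in total.

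The stated figures reproduce as a comparison of two means at one time. No 3-month effect and no within-patient correlation enter.

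**2. Power of the interaction if time is categorical (assumption).** Further assumptions: 77 completers per arm, a random intercept (equal correlation ρ between visits), and SD 11 as the raw SD at each visit. Let d3 and d6 be the arm differences in change from baseline, and s² = 121(1 − ρ).

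- Covariance of the two estimates: (2s²/77) × [[2, 1], [1, 2]].
- Non-centrality of the 2-df test: λ = 77/(3s²) × (d3² − d3·d6 + d6²). Critical value 5.99.
- Example, ρ = 0.5 (s² = 60.5), effects 2.5 then 5: λ = 77/181.5 × 18.75 = 7.95, power 71.5%.
- Example, ρ = 0.5, effects 5 then 5: λ = 77/181.5 × 25 = 10.61, power 83.9%.

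| ρ | 2-df test, 2.5 then 5 | 2-df test, 5 then 5 | 2-df test, 5 then 0 | 6-month change contrast, 5 points |
|---|---|---|---|---|
| 0.3 | 55.9% | 69.2% | 69.2% | 66.4% |
| 0.5 | 71.5% | 83.9% | 83.9% | 80.5% |
| 0.7 | 91.4% | 97.2% | 97.2% | 95.4% |

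The patterns 5 then 5 and 5 then 0 have the same λ, so the overall test cannot tell a lasting effect from one confined to 3 months.

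**3. If time is linear (assumption).** With visits at 0, 3 and 6 months and complete data, the slope weights are −1, 0, +1. The interaction is then exactly the 6-month change contrast (last column), and a 5-then-0 pattern is declared at the 5% error rate only.

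**4. Effect of calculating effect sizes only after significance.** Simulated under the 2-df rule, SD 11, ρ = 0.5, 77 per arm:

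| True effect at 3 / 6 months | Mean 6-month estimate given p<0.05 | Non-significant interactions in which the 6-month contrast has p<0.05 |
|---|---|---|
| 5 / 5 | 5.4 | 26% |
| 2.5 / 5 | 5.8 | 36% |
| 2.5 / 2.5 | 4.2 | 11% |
| 1.25 / 2.5 | 4.6 | 12% |

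The protocol describes SD 11 as twice the baseline SD, so the baseline value is 11/2 = 5.5. Repeating the simulation with SD 5.5 gives about 5.0 for a true 5 (essentially no inflation) and 2.7 to 2.9 for a true 2.5.

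**The case against.** The case on the other side is substantial.

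- **Time coding is open.** A reader might infer that three visits make this a 2-df test. The article does not say so. Separate effect sizes at 3 and 6 months suggest categorical time, but with linear time and complete data both the power mismatch and the 3-month-only scenario vanish. This stands, and limits those parts to a conditional statement.
- **Loss of power is not established.** A reader might conclude that the trial is underpowered. The documents give neither a 3-month effect nor a correlation, and the calculated power falls on both sides of 80%. This stands.
- **Estimates are not said to be withheld.** It is tempting to say that a null trial would yield no effect estimate. Only Cohen's d is conditional. The mixed model produces estimates, and descriptive statistics are planned for all outcome measures. This stands.
- **The economic analysis is unconditional.** The incremental cost-utility ratios with 95% confidence intervals over 6 months, and the budget impact analyses, do not depend on HADS significance. The decision-maker would not be left with nothing. It does not supply the size of the effect on the primary outcome.
- **The test is valid.** One outcome and one overall test at 5% raises no type I error problem, and after a significant result the two effect sizes would reveal a 5-then-0 pattern. This also stands, but it does not help after a non-significant result.
- **Six months is inferred.** The sample size speaks of follow-up in general; only the drop-out allowance names 6 months.

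None of this answers the core point. The condition on significance is written into the plan, so it is not a detail left to an analysis plan that is not shown.

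**Conclusion.** The point holds in a limited form and should be fixed before analysis; it does not make the primary test invalid. Two things follow from the text alone: the planned effect sizes are selected on p<0.05 and not called for in a null trial, and no primary time point is named. It also follows from the reproduced arithmetic that the 80% power belongs to a single two-group comparison and was not calculated for an overall interaction.

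The rest is conditional. With categorical time, 77 per arm and SD 11 as raw SD, power for effects of 2.5 then 5 points is 55.9% to 91.4% over correlations 0.3 to 0.7, and 83.9% for 5 then 5 at 0.5. A 5-point effect present only at 3 months would be declared a difference in effectiveness 84% of the time at correlation 0.5. Under the same 2-df rule at correlation 0.5, a true 6-month effect of 5 would be reported as about 5.4 to 5.8 on average, and a true 2.5 as about 4.2 to 4.6. The inflation would be much smaller if the SD is nearer 5.5.

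**What to change.** In Statistical analysis:

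1. Delete the words that make the effect sizes conditional on a significant interaction.
2. State that the model-based between-group differences in HADS-T at 3 and 6 months will be reported with 95% CIs and standardised effect sizes whether or not p<0.05.
3. Name the 6-month contrast from the same mixed model as the primary test, with 3 months secondary and the overall interaction as supportive description. State that time is categorical, so that the contrast is defined.

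The primary test then matches the sample-size basis: 77 per arm at follow-up and 206 at baseline, with power of about 80% if 11 is the SD of the quantity analysed. The cost is a few sentences, settled before the data are analysed, with no extra patients, visits or data.
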